### Participant exclusion criteria

Potential participants are excluded from the study if they are currently receiving formal psychotherapy for their depression, been diagnosed with a severe and enduring mental health problem, are currently doing at least 30 continuous minutes of moderate intensity physical activity on 5 or more days of the week, score 2/3 on the PHQ-9 [35] suicide risk question, have been prescribed an antidepressant in the month prior to recruitment, have current substance or alcohol addiction, are unable to use written self-help materials in English, or are currently involved in another research study that would make participation difficult.

### Recruitment settings and procedure

Different recruitment strategies have been adopted for the two IAPT services participating in the study to allow comparison of different participant recruitment strategies. In Plymouth, potential participants meeting the inclusion criteria are invited to participate in the study at the end of the initial assessment session by being handed a study invitation pack by their psychological wellbeing practitioner (PWP) undertaking the assessment. In East and Mid Devon, the study invitation pack is posted to all potential participants who have self-referred or have been referred by a health professional into the IAPT service. In both cases, the invitation packs include a study invitation letter, study information sheet, and consent form.

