**Figure 1 F1:**
[figure not shown]
Consort diagram.

Participants are being recruited through two IAPT services [21] located in one rural (East and Mid Devon) and one city based location (Plymouth). Both services are located in the county of Devon, South West of England.

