### Outcome measurement

#### Feasibility outcomes

The feasibility outcomes are related to the aims associated with a pilot RCT [44]. Descriptive comparisons across the primary outcome measures of interest will be made between the two recruitment sites adopting different recruitment techniques. The feasibility outcomes are outlined in Table 1.

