### Statistical analysis

#### Quantitative

For both recruitment settings, participant flow will be summarised using the CONSORT flow diagram adapted for complex interventions [58], reporting recruitment and attrition rates (both treatment and study drop-outs) with 95% confidence intervals. The CONSORT flow diagram will also be adapted to reflect the number of recruitment letters sent, numbers consenting, number randomised, number undertaking intervention, and number of completed outcomes alongside means, standard deviations and frequencies regarding the number of support sessions, session length, and mean number of days between support sessions. All protocol deviations, along with number of missing items on questionnaires, will be reported. Mean and standard deviations for general demographic information will be reported at baseline with assessments conducted at baseline and 4-, 9-, and 12-month follow-up.

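### Each recruitment strategy runs in one service only and the invitation counts start from different populations, so a difference in recruitment can be described but not attributed to strategy

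*Protocol article*

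**What the plan says.** Recruitment settings and procedure (protocol article) gives the purpose of using two strategies: "Different recruitment strategies have been adopted for the two IAPT services participating in the study to allow comparison of different participant recruitment strategies".

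- **Plymouth:** "potential participants meeting the inclusion criteria are invited to participate in the study at the end of the initial assessment session". The practitioner who made the assessment hands over the pack.
- **East and Mid Devon:** "the study invitation pack is posted to all potential participants who have self-referred or have been referred by a health professional". No eligibility filter before posting is described.

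The text below Figure 1 in Study design identifies East and Mid Devon as rural and Plymouth as a city location.

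Feasibility outcomes, under Outcome measurement, states the planned analysis: "Descriptive comparisons across the primary outcome measures of interest will be made between the two recruitment sites adopting different recruitment techniques". The Quantitative part of Statistical analysis covers both settings. It gives recruitment and attrition rates 95% confidence intervals and has the flow diagram show "the number of recruitment letters sent, numbers consenting, number randomised, number undertaking intervention". Table 1 adds, under recruitment feasibility, the numbers assessed, eligible and randomised, with reasons for ineligibility and non-participation.

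Study aims and objectives says that the pilot tests no hypothesis and has no primary outcome.

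**The concern.** Two things stand between these counts and a statement about strategy.

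First, there are two services and one strategy in each. Strategy is completely aliased with service: rural or city setting, local staff, referral mix and access all change together with the invitation method. The article documents one such influence. Under Changes to methods since recruitment began, some potential participants in Mid and East Devon reported difficulty with the treatment location, and more locations were then added. The confidence intervals do not help, because with one service per strategy they cannot contain any between-service variation.

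Second, the earliest count in the reported flow, letters sent, falls at a different point in the pathway at each site. In Plymouth it comes after a practitioner has assessed the patient against the inclusion criteria; in East and Mid Devon it comes before any assessment. The article does not say whether Plymouth patients ruled out before a pack are counted. If they are not, the numbers eligible and the reasons for ineligibility in Table 1 also describe different populations at the two sites.

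Recruitment feasibility is the first outcome in Table 1, and the pilot exists to inform a phase III trial. What is at stake is whether a reader could take a difference in pack-to-participant rates as evidence for one way of inviting patients.

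**Working it through.** The plan gives no recruitment rate, invitation count or precision for this comparison, so there is no figure to reproduce. The check asks how far the choice of denominator alone moves the contrast when nothing about willingness differs between the services.

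**Inputs, all assumed**

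- *e*: share of referrals who are eligible, 0.3 to 0.5, the same in both services.
- *s*: share of Plymouth packs that reach eligible people, 0.6 to 0.8. It is below 1 because telephone screening and the CIS-R confirmation at baseline both come after the pack (Screening, baseline, and informed consent).
- *c*: share of eligible Plymouth referrals actually handed a pack, 0.5 to 1.0.
- *u*: uptake among eligible people who receive a pack, 0.2 in both services.

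Letters sent is read as packs given out, and East and Mid Devon packs are taken to go to every referral.

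**Per pack**

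Plymouth yields *u* × *s* and East and Mid Devon *u* × *e*. The ratio is *s*/*e*, and *u* cancels.

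| | *e* = 0.3 | *e* = 0.5 |
|---|---|---|
| *s* = 0.6 | 0.6/0.3 = 2.0 | 0.6/0.5 = 1.2 |
| *s* = 0.8 | 0.8/0.3 = 2.67 | 0.8/0.5 = 1.6 |

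Plymouth looks better whenever *s* exceeds *e*, by about 1.2 to 2.7 times over this range.

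**Per referral**

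Plymouth yields *u* × *e* × *c* and East and Mid Devon *u* × *e*. The ratio is *c*, which cannot exceed 1. For 1,000 referrals with *e* = 0.3 and *u* = 0.2:

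- East and Mid Devon: 1,000 × 0.3 × 0.2 = 60 recruits.
- Plymouth, *c* = 0.5: 1,000 × 0.3 × 0.5 × 0.2 = 30.
- Plymouth, *c* = 0.8: 1,000 × 0.3 × 0.8 × 0.2 = 48.
- Plymouth, *c* = 1.0: 1,000 × 0.3 × 1.0 × 0.2 = 60.

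**One case on both scales** (*e* = 0.3, *s* = 0.8, *c* = 0.8, *u* = 0.2)

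Plymouth hands packs to 1,000 × 0.3 × 0.8 = 240 eligible people, and so gives out 240/0.8 = 300 packs for 48 recruits: 48/300 = 16% per pack and 4.8 per 100 referrals. East and Mid Devon sends 1,000 packs for 60 recruits: 6% per pack and 6.0 per 100 referrals. Plymouth leads by 16/6 = 2.67 on one scale and trails by 4.8/6.0 = 0.8 on the other, with the same uptake among eligible people in both.

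**The case against.** The strongest reply is that the plan promises little. The between-site comparison is called descriptive, its sentence names site and technique together, and no hypothesis is tested. A reader might infer that the comparison cannot be made at all. That goes too far: two site-plus-strategy combinations can be described. What remains is that the stated purpose is to compare strategies, that no caveat on attribution is given, and that describing a contrast does not remove the aliasing.

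A reader might also infer that the plan is bound to favour Plymouth. The article does not support that. Letters sent is one count among several and the recruitment rate is not defined as per letter. The advantage exists per pack, other things equal; per referral it disappears or reverses, and real differences between services could push either way. Nor is the Plymouth pre-screen complete, so a ratio of 1/*e* would overstate the effect.

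Most of the later counts are already planned, and if every East and Mid Devon referral receives a pack, letters sent there approximates referrals. That stands. The main gap is Plymouth before the invitation.

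Finally, the phrase about primary outcome measures can plausibly mean the Table 1 feasibility measures, since the next sentence in that section points there. It does not show that clinical outcomes will be used to judge recruitment. It is still loose wording in a trial that says it has no primary outcome.

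**Conclusion.** The point holds in a limited form. With one strategy per service, a difference in recruitment cannot be attributed to strategy; this follows from the design and needs no assumption. Rates per pack rest on different populations and, at equal uptake, would look about 1.2 to 2.7 times higher in Plymouth under the assumed shares, while rates per referral would be equal or lower there. The sizes are illustrative, because the article gives none of the shares. The firm conclusion is that the apparent ranking depends on a denominator the plan does not fix.

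Two further inferences are not supported. No section says that phase III will choose its recruitment route from this contrast, and no progression criteria are set. The randomised comparison of arms is not affected: participants are randomised individually and recruitment site is a minimisation factor. This is an inexpensive improvement to what the pilot can conclude on its first feasibility outcome.

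**What to change.** 1. **One denominator.** Report participants randomised per 100 referrals into each service over the same calendar period. For each service show the numbers referred, assessed, eligible, invited, responded and randomised, including Plymouth patients ruled out before a pack was given, where service records allow.
2. **Recruitment settings and procedure.** Replace the stated purpose with: *The two services use different invitation methods; recruitment will be described under each combination of site and strategy, and differences will not be attributed to strategy.*
3. **Feasibility outcomes.** In place of the phrase about primary outcome measures, name the recruitment and retention measures of Table 1 that will be compared between sites.

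The cost is obtaining referral and assessment counts from the two services, a few changed sentences, and a weaker claim. Alternating the strategies within each service would separate strategy from site, but with 60 of 80 participants recruited at the time of writing that is realistic only for a later study.

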### Screening, baseline, and informed consent

Potential participants willing to consider participation are asked to contact the researcher directly by phone or mailing the consent form (Additional file 2) with their contact details. Any further questions about the trial are answered on the phone and, if participants wish to participate, they are asked to provide verbal consent for a telephone screening informed by the inclusion criteria to assess eligibility for study inclusion. Following screening, and after gaining written consent, eligible participants are invited to attend a full baseline appointment with the researcher using the CIS-R [32] to confirm a diagnosis of major depression with participant randomisation undertaken following baseline assessment.

### Confidentiality

All personal data held electronically is stored on a password protected computer at the University of Exeter. Personal data held on paper files are locked in a filing cabinet at the University of Exeter, with the researcher being the only person with access to the key. All the information will be safely stored in line with the principles of the Data Protection Act. PWPs operating within the respective IAPT Services will follow guidance for Good Clinical Practice. Consistent with good clinical practice and detailed in the consent form, significant suicidal risk identified will be discussed with the participant and the GP will be informed. The consent form will also let the person know that, if we are very concerned about their safety or someone else’s safety, we would need to break confidentiality.

### Randomisation

A web-based minimisation service supported by the Peninsula Clinical Trials Unit ensures concealment allocation of participants to a PWP who has either been trained to deliver BA as usual or BAcPAc. To preserve researcher blinding regarding the study arm participants are randomised into, the Peninsula Clinical Trials Unit sends an e-mail containing randomisation details for the participant to the IAPT service administrator and a PWP supporting the intervention within that service. At the same time, the participant’s ID number with no other personal information is also e-mailed to the researcher.

Minimisation is based on the following prognostic factors: participant age (10–30 years or >31years), sex (male or female), PHQ-9 [35] score (moderate/moderately-severe 10–18; moderately-severe/severe 19–23), current use of anti-depressant medication (yes or no), and recruitment site (Plymouth or East and Mid Devon). To maintain concealment, the minimisation algorithm retains a stochastic element, providing a degree of unpredictability during the allocation process. The first participant was randomised on the 23^rd^ of April 2013.

### Sample size

A total of 80 participants (40 participants per arm) will be recruited. This sample size has been informed by the recommended sample size of ~30 participants per arm for estimation of outcome variance [36] and takes into account a 20% attrition rate over the duration of the study.

### Treatments

For both the BAcPAc (intervention) and BA alone (TAU) study arms, the BA protocol was developed by Richards [17] and represents the protocol implemented as part of the IAPT programme [21,22]. In the BA alone study arm, the BA protocol [17] has been directly transferred into a written self-help format specifically developed and adopted for use within the study (available on request from the authors). The patient works through the written self-help intervention with a maximum of 12 support sessions provided by a PWP [37]. In the BAcPAc study arm, the BA protocol [17] formed the foundation of an extensive development process based upon focus groups and informed by intervention mapping techniques [17] to deconstruct the BA protocol, and then to reconstruct it within a written self-help intervention [37] incorporating additional PA promotion techniques (available on request from the authors).

Interventions are delivered by four PWPs in both recruitment sites, with two randomised to deliver the BAcPAc study arm and two BA alone in both sites. The PWP role was developed as part of the IAPT programme to support low-intensity CBT interventions within a stepped care model of service delivery for patients presenting with depression and anxiety disorders (excluding PTSD and social anxiety) of mild-to-moderate severity [37]. All PWPs involved in the study have successfully completed an accredited PWP training programme based upon the curriculum [38] developed for the IAPT programme.

Furthermore, study PWPs also received an additional one-day training session delivered by members of the research team. The training introduced the PWPs to the study and provided them with the opportunity to address any questions. Additionally, procedures for working within the trial, including recording sessions and maintaining records on patient contacts, were reviewed. The training additionally overviewed the self-help intervention and theoretical rationale, appropriate to the study arm they were randomised to support. For PWPs in both study arms training used role-play to enhance skill development in supporting the appropriate self-help intervention. For PWPs supporting the BAcPAc intervention this also included skills enhancement in PA promotion techniques (Figure 1), included within the self-help intervention. Training sessions also provided the opportunity to ask any questions concerning the intervention protocols. PWPs supporting BAcPAc (Additional file 3) and BA alone (Additional file 4) are given a training manual to supplement the training received. During the course of the study, PWP supervision was conducted in accordance with IAPT supervision guidance [39]. Supervisors in the BAcPAc arm have also been provided with the BAcPAc intervention and encouraged to contact a member of the research team to answer any questions about the intervention or to raise questions emerging from the supervision sessions.

As with any pragmatic study, interventions in both study arms are delivered in accordance with the IAPT service delivery protocol developed to inform the delivery of low-intensity CBT interventions, including CBT self-help [37]. Consistent with this protocol, the number and length of support sessions in both study arms is not specified in advance, but determined collaboratively between the PWP and patient on the basis of any change in the patient’s depressive symptoms. Alternatively, participants are free to stop treatment or withdraw from the study at any time. In the case of a participant disclosing immediate suicidal risk to a PWP or researcher, the risk protocol will be followed and the participant will be withdrawn from the study.

Typically, participants receive one assessment session of up to 35 minutes followed by up to 12 support sessions of 25–35 minutes [37], with an average of 5.5 used within the IAPT programme [22]. The assessment session largely comprises a client-centred assessment to understand the difficulties experienced by the participant, administration of questionnaires to measure severity of depression, anxiety, and impact of mental health difficulty on work and social adjustment, alongside the provision of information concerning the wider impact of depression. Additionally, during the assessment session, participants are introduced to the written CBT self-help intervention related to the study arm they have been randomised into. Participants in the BAcPAc arm are given the BAcPAc written self-help intervention [40], whilst those in the BA alone arm are given the BA written self-help intervention [41]. Participants in both study arms are also given written gender-specific case studies that introduce the BAcPAc or BA alone intervention.

Subsequent support sessions are based around identifying the participant’s progress on the use of the specific written CBT self-help intervention developed for their study arm and provide guidance and encouragement to support the participants’ continued usage of the written self-help intervention. In the event the participant struggles with any activity detailed in the written CBT self-help intervention, the PWP reviews the intervention with the participant to enable him/her to problem-solve the difficulty and provide motivation to enable them to move forward with the intervention before the next support session. Dependent upon participants’ preference, support is provided face-to-face, over the phone, or through a combination of both methods. Furthermore, if requested, face-to-face sessions take place in a variety of locations including the participating IAPT service or GP surgery attached to the IAPT service.

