### Study aims and objectives

Informed by the new Medical Research Council (MRC) framework for the development of complex interventions [31], the protocol for a phase II pilot randomised controlled trial (RCT) is reported. This study will examine a number of methodological uncertainties to inform the conduct of a phase III RCT to assess the clinical and cost-effectiveness of a combined BA and PA promotion intervention (BAcPAc) to reduce depressive relapse and improve physical health outcomes for adults with depression compared to BA alone, which represents treatment as usual. No prospectively-identified criteria for progression to a main trial have been set.

This pilot RCT does not involve any hypothesis testing and therefore there is no primary outcome. We are interested to test recruitment and retention rates as well as gain qualitative feedback on feasibility and acceptability of the methodology. The specific feasibility outcomes with the method of evaluation for this pilot RCT are shown in Table 1.

**Table 1 T1:** Feasibility outcomes and evaluation

**Feasibility outcomes**	**Evaluation**
1. Feasibility of participant recruitment	Numbers assessed for eligibility, numbers eligible, reasons for ineligibility, reasons for non-participation, and numbers randomised
2. Appropriateness of data collection processes and outcome measures	Number of missing items and follow-up rates
3. Participant understanding of study information	Qualitative process interviews with participants following participation
4. Estimation of sample size to inform a phase III RCT	Differences at follow-up between study arms in the number of participants that reach an ICD-10 diagnosis of depression using the CIS-R [32]
5. Level of study attrition	Study and treatment drop-out rates
6. Estimate of the resources and costs needed to deliver the intervention	Variability in the number, length, and frequency of support sessions provided by psychological wellbeing practitioners
7. Acceptability towards the cognitive behavioural therapy self-help intervention received, and engagement with the BAcPAc intervention	Qualitative process interviews undertaken with participants following participation

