**Figure 2 F2:**
[figure not shown]
Intervention processes.

i) The rationale for the intervention is altered to emphasise and reinforce the added value of activities that include a PA component.

ii) Principles derived from self-determination theory [24,26] are used to inform the development of the BAcPAc self-help intervention. In particular, this was used to adapt the text and content of the support provided by the PWP to help motivate and engage participants to maintain and develop plans to initiate more activities that involve sustainable PA into their normal weekly planning.

iii) If the PWP identifies participant mood starting to improve during treatment he/she encourages the participant to further increase PA using principles informed by self-determination theory [24] alongside techniques derived from motivational interviewing [42]. This helps maintain participant motivation to continue with the PA identified as part of the standard BA aspect of the intervention.

iv) The diary keeping elements of the BAcPAc self-help intervention were adapted to specifically prompt the participant to continue to monitor and plan their PA using the worksheets included within the intervention.

v) On occasions when the participant has planned PA involving walking within their diary, the PWP encourages the participant to use a pedometer [43] and record the number of steps taken per day on the appropriate worksheets included within the BAcPAc self-help intervention.

vi) Finally, unlike participants in the control arm, those randomised to the BAcPAc arm receive a 10–15 minute follow-up phone call by the PWP one month after the end of treatment at a time agreed between the PWP and participant during the last support session. The aim of this appointment is to review progress with the BAcPAc self-help intervention and support the participant to continue with PA by encouraging them to continue to self-monitor PA using diaries and/or pedometers, problem-solve any difficulties, and resume the BAcPAc self-help intervention and case studies if they identify any worsening of mood.

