### Data collection

The researcher collects general demographic information during telephone screening. All other data informing the feasibility outcomes is extracted from routine service records by the PWP delivering the intervention at the end of the support session, by the researcher during 4-, 9-, and 12-month follow-up, or from process interviews. All participants will be followed-up despite any deviation from planned treatment. Time points representing collection of the assessments are highlighted in Table 2.

**Table 2 T2:** Assessments administered at screening, baseline, and follow-up post-baseline

	**Screening**	**Baseline**	**4 months post baseline**	**9 months post baseline**	**12 months post baseline**
PHQ-9	X		X	X	X
CIS-R	X		X	X	
Physical activity					
7 day PA recall		X	X		
Accelerometer			X	X	
Body mass index		X	X	X	
Blood pressure		X	X	X	
Health and social care service use (ADSUS)		X	X	X	
Sleep-insomnia severity index		X	X	X	
Quality of life					
SF-36		X	X	X	
EQ-5D		X	X	X	

Assessments taken at baseline are collected face-to-face or over the telephone depending upon patient preference, with height, weight, and blood pressure collected face-to-face. All data collected at 4-month follow-up is collected face-to-face, with 9 and 12 month follow-up data collected face-to-face or over the phone, depending on patient preference. Adverse events are reported by PWPs to the researcher during routine communication and spontaneously. The researcher inquires of any adverse events at follow-up. Any events are recorded and escalated to the PI, and if necessary, to the sponsor.

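### Withdrawal from the study on disclosure of immediate suicidal risk is not reconciled with follow-up of all participants, so outcome data could be lost for a reason tied to the outcome

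*Protocol article*

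**What the plan says.** The Treatments section sets the rule for immediate suicidal risk, whether it is disclosed to the practitioner or to the researcher. The stated consequence is that "the risk protocol will be followed and the participant will be withdrawn from the study". The sentence before it treats leaving treatment and leaving the study as two different things: "participants are free to stop treatment or withdraw from the study at any time". The risk rule then uses the study-level term.

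The Data collection section says: "All participants will be followed-up despite any deviation from planned treatment". It names no exception. The Confidentiality section also deals with suicidal risk. It provides for discussion with the participant and notice to the GP, and does not mention withdrawal.

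Two feasibility outcomes in Table 1 depend on who is followed up. Item 4, which informs the phase III sample size, is evaluated by "Differences at follow-up between study arms in the number of participants that reach an ICD-10 diagnosis of depression using the CIS-R". Item 5, study attrition, is evaluated by "Study and treatment drop-out rates". The Quantitative part of Statistical analysis plans "reporting recruitment and attrition rates (both treatment and study drop-outs) with 95% confidence intervals".

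**The concern.** The two statements give staff no clear answer to a practical question: is the next follow-up assessment still due for a participant who was withdrawn under the risk rule?

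If the answer is no, the loss is not random. The trigger is a marker of severe depression, and depression is what the CIS-R and PHQ-9 measure. Disclosure may be made to the researcher as well as to the practitioner, and the PHQ-9 used at follow-up has a suicide risk question. An assessment at 4 months could therefore prompt the exit that removes the later ones. Participants lost in this way would tend to be cases, so the observed proportion with a diagnosis and the mean PHQ-9 would look better than the truth.

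A second consequence concerns retention. Exits imposed by the protocol would count as study drop-outs alongside participants who chose to leave. The two carry different information for phase III: one reflects a rule that can be rewritten, the other reflects acceptability. The pilot tests no hypothesis, but these estimates are part of what it is meant to deliver.

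**Working it through.** **Side by side.**
- Treatments: trigger is disclosure of immediate suicidal risk; consequence is withdrawal from the study; no statement on outcome data.
- Data collection: applies to all participants; covers any deviation from planned treatment; no exception stated.
- Confidentiality: covers significant suicidal risk; no withdrawal mentioned.

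The article never says whether outcome collection continues after a risk withdrawal.

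**Plan's own figure.** Sample size section: about 30 per arm wanted, 20% attrition, 40 per arm recruited. Check: 30/(1 − 0.20) = 37.5, so 38 per arm, close to the stated 40. In reverse, 40 × 0.80 = 32 assessed per arm. This figure is not in dispute and serves only as the base below.

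**Effect on the depression rate (illustration).** The documents give neither a disclosure rate nor a follow-up case rate. Assume that 32 per arm would be assessed without forced exits, that d of them are true CIS-R cases, and that k exits occur, all of them cases. Observed rate = (d − k)/(32 − k).

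| k | True 16/32 = 50.0% | Bias (points) | True 10/32 = 31.3% | Bias (points) |
|---|---|---|---|---|
| 1 | 15/31 = 48.4% | −1.6 | 9/31 = 29.0% | −2.2 |
| 2 | 14/30 = 46.7% | −3.3 | 8/30 = 26.7% | −4.6 |
| 3 | 13/29 = 44.8% | −5.2 | 7/29 = 24.1% | −7.1 |
| 4 | 12/28 = 42.9% | −7.1 | 6/28 = 21.4% | −9.8 |

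**If the exits already sit inside the 20% allowance.** Then 32 are still assessed and the k lost cases are added back: true rate = (16 + k)/(32 + k) against an observed 16/32 = 50.0%. For k = 1, 17/33 = 51.5% (bias −1.5 points). For k = 2, 18/34 = 52.9% (−2.9). For k = 4, 20/36 = 55.6% (−5.6). The direction is the same and the size slightly smaller.

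**Against sampling error.** For one arm at 50%, the standard error is √(0.5 × 0.5/32) = 8.8 points, so the 95% half-width is about 1.96 × 8.8 = 17 points. The illustrated bias lies well inside that.

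**Effect on attrition.** Each forced exit beyond the 16 of 80 implied by the 20% allowance adds 1/80 = 1.25 points. Wilson 95% intervals:
- 16/80 = 20.0% (12.7 to 30.0)
- 18/80 = 22.5% (14.7 to 32.8)
- 20/80 = 25.0% (16.8 to 35.5)

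Forced exits push attrition up.

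**The case against.** The best defence is that the follow-up promise is worded around deviations from treatment. It cannot cover every departure, because participants may also leave the study when they wish. On that reading, study withdrawal lies outside the promise and the two statements coexist. The risk protocol is not shown and may define the term. This has force, and outright contradiction is more than the text proves. The exception is still unwritten, and the follow-up sentence speaks of all participants.

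The event is also likely to be rare. The trigger is immediate risk, and anyone scoring 2 or 3 on the PHQ-9 suicide question is excluded at entry. This stands, and it limits the size.

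A reader might infer four stronger points that the documents do not support.
- **Attrition hides these participants.** It does not. They count as study drop-outs and raise the rate.
- **Withdrawals will differ by arm.** Participants in the intervention arm have one additional contact, since "those randomised to the BAcPAc arm receive a 10–15 minute follow-up phone call by the PWP one month after the end of treatment". That is one short call beside an assessment, up to 12 support sessions and three researcher follow-ups common to both arms. Nothing shows that it would yield more disclosures, so any between-arm bias figure would rest on invented counts.
- **Safety information on the event is lost.** Practitioners report adverse events to the researcher, who records and escalates them, so the disclosure itself has a reporting route. Only later enquiries would be lost, and only if withdrawal ends data collection.
- **The retention estimate is wrong.** If phase III kept the same rule, these exits would be real losses to plan for. The fault is that two kinds of exit are combined.

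**Conclusion.** The concern holds in a limited form. The article imposes study withdrawal in one section and promises follow-up of all participants in another, without saying how they fit together. If withdrawal ends outcome collection, later CIS-R and PHQ-9 data go missing for a reason tied to the outcome. The bias is towards better outcomes, and mandated exits are mixed with chosen ones in study attrition.

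The direction follows from the trigger. The size does not come from the documents. The illustrated 1.6 to 7.1 points at a true 50% rate assumes 1 to 4 exits per arm, all of them cases, and that count may be high given the entry exclusion. The effect is probably small beside the sampling error of a pilot of this size. Severity is minor to moderate. No view is taken on the clinical rule.

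**What to change.** 1. Reconcile the Treatments and Data collection statements. Leave clinical handling, including whether study treatment stops, to the risk protocol.
2. State that withdrawal under this rule does not by itself end outcome data collection where the participant still consents to it.
3. In the participant flow and attrition summaries, show protocol-mandated withdrawals separately from participant-chosen drop-out.
4. Optionally, add a sensitivity summary that counts mandated withdrawals without follow-up as CIS-R cases.

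The cost is a short wording amendment, one extra line in the flow diagram and, if wanted, one extra row in a table. No visits are added beyond those already planned. The abstract reports 60 of the planned 80 recruited at the time of writing, so a prompt clarification could still affect what is collected.
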